# Statistical analysis

Primary analyses

The are two planned primary analyses:

1) Superiority of treatment completion: treatment completion is defined as taking at least 80% of the recommended doses within 120% of allowed time. Since this is a dichotomous outcome, this primary analysis will be a logistic regression, using an identity link, and estimated via generalized estimating equations to account for clustering by household. An exchangeable correlation structure and empirical standard errors will be used. We will compare the proportion having treatment completion in each high dose arm against the standard arm – 10 mg/kg/day rifampin given for 4 months.

Given that some exclusion post randomization could occur (for example, contacts are enrolled, but the DST results of their index case were not available at the randomization, then later the DST shows resistance to rifampin), a modified intention to treat analysis will be used – with these valid post-randomization exclusions not included in the primary analysis. A secondary analysis will be done among patients who completed therapy per protocol.

2) Non-inferiority of safety: analysis of grade 3-5 adverse events will be as for relatively rare dichotomous outcomes. Poisson regression will be used to compare the occurrence of the grade 3-5 adverse events between each of the two experimental arms and the conventional arm. To account for clustering by household, we will use Generalized Estimating Equation (GEE), with an exchangeable correlation structure and empirical standard errors. To assess non-inferiority, we will use the confidence interval approach, and compare the upper limit of the difference versus a margin of 4%.

Secondary analyses:

Non-inferiority of completion. A planned secondary analysis will assess non-inferiority of completion. The maximum allowable (maximum tolerated) difference will be **5%, with one-sided significance level.**  With the number of participants we expect to enroll for the primary analysis (1359), we will have 80% power to show non-inferiority if any of the experimental arms has 5% higher completion than the control arm, assuming the completion in control arm will be between 70 and 80 % (as it was in the previous RCT).

- We will compare the occurrence of grade 1-2 adverse events reported by study investigators and judged by the independent blinded adjudication panel to be possibly or probably related to study drug in the same way as grade 3-5 adverse events.

- Active TB – the incidence of active TB (microbiologically confirmed and all forms) in the 26 months post-randomization per 100 person-years of follow-up will be compared between all three arms.

All analyses will include adjustment for clustering by household. In stratified analysis, results will be presented by indication for LTBI treatment. Sensitivity analyses will be conducted where by analysis are stratified by study centre and by country.

Interim analyses

To optimize protection of safety of study participants, we plan at least two interim analyses of study regimen completion and of Grade 3-5 adverse events. The first analysis will be conducted after the first 150 participants randomized (i.e. approximately 50 in each arm) have completed therapy. This means we will assess outcomes that have occurred in each of these individuals up to 146 days post-randomization. The second interim analysis will be conducted 146 days after randomization of the 450^th^ Participant – i.e. after approximately 150 participants should have completed therapy in all 3 arms. However, as described below, the 2^nd^ analysis may be performed sooner if there are concerns about excess toxicity with either high-dose arm.

Our goal is to identify as early as possible if the high dose rifampin regimens are associated with a clinically important increased rate Grade 3-5 AE, or intolerance – defined as failure to complete therapy. The study bio-statistician will conduct both interim analyses in a blinded fashion. Given that there are two planned interim analyses, the p value -adapted for multiplicity of testing- that will be used to consider significant the difference between proportions is of p<0.022 (Pocock’s method).The Data Safety and Monitoring Board (DSMB – see below for more details) will also consider results while remaining blinded to the identity of the regimens. For each interim analysis, if any of the regimens meets criteria for a clinically important difference in adverse events or completion, then we will unblind in step-wise fashion. If unblinding is deemed necessary, the person in charge of code breaking will be the principal investigator ([name]) and the study coordinator ([name]). Same procedures will be followed if DSMB asks for unblinding in specific cases for serious and unexpected adverse events.

Most clinical trial experts do not suggest formal statistical stopping rules for safety. Instead, the DSMB will receive frequent safety reports and will “make judgments about the strength of the evidence and the absolute magnitude and seriousness of any safety signals” (Pocock, Clayton, and Stone 2015). As approximate guidance, we will suggest to the DSMB that for the 1^st^ interim analysis non-completion must be at least 10% worse and/or grade 3-5 adverse events more than 10% more frequent than the standard arm. For the 2^nd^ interim analysis occurrence of grade 3-5 adverse events would have to be 7.5% worse, and treatment completion at least 7.5% worse to consider dropping that arm. Grade 3-5 adverse events are very uncommon events with 4R (1-2% in our prior trials), meaning that we expect zero or only one AE in the standard arm with 50 participants. Hence occurrence of Grade 3-5 AE in only 5 or 6 of the first 50 participants randomized to either experimental arm would result in an AE rate difference of 10% for the 1^st^ interim analysis. This could happen due to chance alone. At the 2^nd^ interim analysis – we expect 2-3 persons with Grade 3-5 AE among the 150 randomized to 4R_10;_ to detect a difference of 5%, would mean at least 9-10 participants in the highest dose arm would have to have Grade 3-5 AE, or 18-20 participants with these AE in both high dose arms, before stopping the trial; this number with AE would be very unlikely due to chance alone. But, as noted above – these are guidelines only that will be suggested to the DSMB. The decision to stop enrolment to one or both experimental arms will be based not only on these differences, but also how serious the adverse events are. The threshold to stop will be lower if the events are more serious. As well, the DSMB can request more frequent analyses of adverse events – if there is any evidence on greater rate of AE with the higher dose arms.

We also do not wish to unblind the DSMB unnecessarily as this can bias the DSMB decisions. First, we will reveal if the arm with higher rate of AE/lower rate of completion is the standard 4 month arm. If so, we will not reveal the identity of the other two arms, and enrolment to all three arms will continue. If the arm with substantially higher rate of events of Grade 3-5 AE or non-completion, is one of the two experimental arms then we will reveal the identity of all three arms to the DSMB. If the 30 mg/kg arm has the excess events, but not the 20 mg/kg arm – then we will stop enrolment to the highest dose arm. On the other hand, if the 20 mg/kg arm has the excess events, but not the 30 mg/kg arm, this will be considered more likely due to chance (since it is biologically less plausible). In this situation we will combine results from the two high dose arms, to determine if the combined outcomes are considered a clinically important difference in AE or completion compared to the standard arm. If the DSMB believes these criteria are met – then enrolment to the trial will stop, and we will report results.

The criteria to conclude that an experimental arm has higher rates of Grade 3-5 AE or non-completion that are clinically important (the “stopping rules”) will be different for the two interim analyses, as we want to guard against a ‘false positive’ results. We wish to avoid concluding incorrectly that a high dose regimen has excess toxicity, and therefore stopping enrolment. One safeguard against falsely concluding the rate of non-completion is worse with the high dose regimens is that completion should be better, since the regimen is shorter. Hence if it is actually worse, then the most important presumed benefit of the regimen is actually not achieved. (*Interestingly, the infamous 2RZ regimen described earlier* ***did not have better completion rates*** *than the much longer comparator regimens of 6H or 12H (Gao et al. 2006) – a potentially important warning of the 2RZ regimen’s poor tolerability. This finding was ignored in 2000, but recognized a year later in the ‘post-mortem’ analyses of the 2RZ failure*).

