# Outcomes

## Primary outcomes

The study has two primary outcomes: regimen completion and safety

Regimen completion: we have selected regimen completion as one of the two primary outcomes because we consider this to represent a summary measure of tolerability – i.e. the combined impact of patient decision to stop due to symptoms, such as stomach upset, anorexia, or fatigue, and health care provider decision to stop based on objectively measured events such as rash, or liver or hematological toxicity. This outcome has the additional advantages of being easy to define and measure, and does not require the added judgment of investigators, or an outside panel. Treatment completion is also readily comparable to completion measured in other studies.

This outcome will be based on the number of pills dispensed and pill counts during treatment phase follow-up visits. For the 2-month high-dose rifampin regimens, treatment phase medical follow-up visits by patients will be made two weeks after the start of therapy, at 4 weeks, and at end of therapy, and for 4R_10_ after 1 and 2 months and at end of therapy (total 3 follow-up medical visits for each regimen). Completion will be defined as taking 80% of doses within 120% of allowed time (48 doses within 72 days for the two-month regimens, and 96 doses within 144 days for the 4-month regimen).

Safety: Grade 3 to 5 adverse events (and Grade 1-2 rash) which result in permanent discontinuation of the study drug, and that are considered probably or possibly related to the study drug by the majority of a three-member independent and blinded Adverse Events panel. This panel (see below for details on panel) will review all events when the study investigator / primary health care provider stopped the study drug permanently because of their concerns of a potential drug-related adverse event. The panel will review these incidents blinded to rifampin dose, and independently from each other. Grading will be standardized using criteria established by the American Thoracic Society for hepato-toxicity (Saukkonen et al. 2006) and the National Cancer Institute for all other adverse events (National Cancer Institute Terminology Criteria for Adverse Events v4.0, at: <https://evs.nci.nih.gov/ftp1/CTCAE/CTCAE_4.03/Archive/CTCAE_4.0_2009-05-29_QuickReference_8.5x11.pdf>

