This trial will have several mechanisms to ensure the safety of study participants. During treatment phase participants will be followed closely with regular visits at which questions are asked about occurrence of new symptoms as well as laboratory monitoring as described above. All new symptoms will be recorded and managed with appropriate follow-up by the treating team. Participants will also be encouraged to call or visit the study centre if they experience any new symptoms. If at any time during treatment (up to 30 days after end of treatment) an adverse event is suspected by study staff, or treating team, this will be investigated, managed and reported following strict protocols that vary according to the type of adverse event. (Note: for possible adverse events occurring after end of treatment, investigations needed and reporting is decided on a case by case basis by site investigator and coordinating center). Adverse events of grade 3 or 4; and rash of any grade, that are considered possibly or probably drug-related will require study medication **permanent discontinuation**. Providers may, on an individualized basis, decide to continue or restart the study drug if the AE was a mild rash (Grade 1-2) or an alternate explanation was found. For example, another drug or food was ingested that could have caused the rash. In these circumstances close follow-up (i.e. daily or every other day) is required and if the rash worsens, management should be re-evaluated.

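### The planned secondary analysis of treatment completion is restricted to completers, so it returns 100% in every arm and carries no information

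*Protocol*

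**What the plan says.** Item 1 of the primary analyses in the Protocol's Statistical analysis section concerns superiority of completion. It sets the outcome as follows: "treatment completion is defined as taking at least 80% of the recommended doses within 120% of allowed time". Primary outcomes gives the same rule with its thresholds: "48 doses within 72 days for the two-month regimens, and 96 doses within 144 days for the 4-month regimen".

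The primary analysis of item 1 is modified intention to treat, "with these valid post-randomization exclusions not included in the primary analysis". The next sentence, still within item 1, reads: "A secondary analysis will be done among patients who completed therapy per protocol". It names no other outcome, and the protocol defines no other per-protocol set.

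Item 2 (non-inferiority of safety, 4% margin) names no supportive population. The planned secondary analysis of non-inferiority of completion (5% margin) and the active TB analysis also name no population of their own.

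**The concern.** A secondary population is useful when it shows whether the primary result holds under a different, defensible choice of who is counted. Here the rule for entering the set is the outcome being compared. Everyone admitted has completed and everyone who failed is left out, so the arms cannot differ.

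This matters because completion is one of two primary outcomes and is the protocol's overall gauge of how well the regimens are borne ("we consider this to represent a summary measure of tolerability"). The one alternative population named for it cannot support or question the main result. The protocol is not silent here: it states a rule, and an analysis plan that follows the rule inherits an analysis that cannot be run.

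**Working it through.** **1. The plan's own figure.** Inputs from Sample size considerations and Table 2: completion 75% versus 85%, alpha 0.05 (two-sided reproduces the table), power 80%, intra-class correlation 0.33, 4 contacts per household, 65% household contacts, 10% allowance.

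- Unclustered n per arm, unpooled variance: (z₀.₉₇₅ + z₀.₈₀)² × [0.75×0.25 + 0.85×0.15] / 0.10² = 248 after rounding up. The table has 247.
- Design effect: 1 + (4 − 1) × 0.33 = 1.99. Then 247 × 1.99 = 492; the table has 493.
- Mixed population: 0.65 × 493 + 0.35 × 247 = 407; the table has 412, within 3%.
- Allowance: 412 × 1.10 = 453 per arm, and 3 × 453 = 1359.

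The planning figures reproduce closely enough to use 412 per arm below.

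**2. Completion in the two populations.**

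| Population | 4R10 | Each high-dose arm | Difference |
|---|---|---|---|
| Modified intention to treat | 412 × 0.75 = 309, so 309/412 = 75% | 412 × 0.85 = 350, so 350/412 = 85% | 10 points |
| Completers only | 309/309 = 100% | 350/350 = 100% | 0 |

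In the second row the variance p(1 − p) is 1 × 0 = 0 in every arm, so there is no effect to estimate and no test. The row reads the same for any true completion rates. For the 5% non-inferiority analysis of completion, a difference fixed at 0 would always lie inside the margin.

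**3. What would happen if the set were carried over to safety.** A primary safety event is one of those "which result in permanent discontinuation of the study drug, and that are considered probably or possibly related to the study drug". The section on methods to ensure participant safety makes permanent discontinuation the rule: "Adverse events of grade 3 or 4; and rash of any grade, that are considered possibly or probably drug-related will require study medication" to be stopped for good, with individual exceptions allowed for mild rash or where another cause is found. A participant stopped before dose 48 (two-month arms) or dose 96 (4R10) cannot be a completer. Only events after 80% of doses can stay in the set.

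The protocol does not say when events occur, so the share retained is an assumption. Let onset follow an exponential decline at rate k per course. The share falling after 80% of doses is (e^(−0.8k) − e^(−k)) / (1 − e^(−k)), and 0.20 when k = 0.

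| Assumed onset | Share retained | Share excluded |
|---|---|---|
| Even over doses (k = 0) | 20% | 80% |
| k = 1 | 13% | 87% |
| k = 2 | 8% | 92% |
| k = 3 | 4% | 96% |
| k = 5 | 1% | 99% |

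At event rates of 1% to 3% (the 4R10 rates in Table 3), 412 per arm gives 412 × 0.01 = 4.1 to 412 × 0.03 = 12.4 events. With even onset, 0.8 to 2.5 per arm would remain.

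Two facts bear on timing. The scheduled on-treatment blood tests, at 2 weeks (high-dose arms) and one month (all arms), come before the 80% point in every arm, which favours earlier detection. The last treatment visits, at 8 weeks (8 × 7 = 56 days) and 16 weeks (16 × 7 = 112 days), come after dose 48 or 96 for someone who misses none, so some late events could remain.

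**The case against.** The strongest reply is that the consequences are small. The modified intention-to-treat analysis, the safety test, the sample size, the interim guidance and the choice of dose for phase 3 do not refer to completers. A table showing 100% in every arm would be recognised at once and could not produce a false claim of superiority. The working definition of a per-protocol set is also commonly left to the statistical analysis plan, which is not shown. All of this limits the weight of the point. It does not remove it, because the protocol gives a rule and the rule fails for the outcome it is attached to. Reading the phrase more strictly than the 80% threshold does not help, since a stricter set is still made up only of completers.

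A second reply is that a completer analysis makes sense for active TB. It would not be circular there, but it would still select on behaviour after randomisation. The sentence stands under completion, so that reading requires moving it.

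A reader might go further and infer that the plan will judge safety among completers and so find non-inferiority whatever the toxicity. The documents do not support this. The sentence is not attached to item 2, and no supportive population is planned for safety. A reader might also infer that nearly all safety events would vanish. That depends on onset times the protocol does not give; with even onset a fifth would remain. Nor can one argue from these documents that people who never took the drug materially dilute the safety difference. No number of non-starters is given, and those told not to start because of disqualifying baseline tests are already valid post-randomisation exclusions.

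**Conclusion.** The point holds for completion. As written, the secondary analysis under item 1 selects on its own outcome and gives 100% against 100% with zero variance. This follows from the protocol's definitions and needs no assumption; 309/309 and about 350/350 only illustrate it at the planning rates.

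The loss of safety events (80% with even onset, up to about 99% under the earliest onset assumed above) is conditional on the set being reused for safety and on assumed timing. It is a reason to rule that use out in writing, and not a fault in the safety analysis the protocol plans. The same applies to the 5% non-inferiority analysis of completion.

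The modified intention-to-treat primary analysis, the safety test and the sample size stand.

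**What to change.** 1. In item 1, delete the completer population for the analysis of completion and keep modified intention to treat as primary.
2. If a supportive analysis of completion is wanted, define a per-protocol set that does not depend on finishing, for example participants who met the eligibility criteria and were dispensed the regimen they were allocated. Supplies are refilled visit by visit, so tie this to the first supply; requiring the full course would bring the circularity back.
3. If participants who never collected or took a dose are left out, call it a sensitivity analysis and report non-starters by arm. Not starting is itself non-completion, and participants know whether they have two months or four, so it may differ between arms.
4. State that the completer set is not to be used for the 5% non-inferiority analysis of completion or for safety.
5. If the sentence was meant for active TB, move it there and label it a selected, non-randomised comparison.

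The cost is wording in the protocol and the statistical analysis plan. Eligibility data, dispensing logs and pill counts are already planned, so no new data, visits or participants are needed.

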We want to detect whether the 2R_20_, and 2R_30_ regimens are *not worse* than 4R_10_ in terms of serious adverse events (SAE) that are plausibly related to the study drugs, as defined above. Hence this requires a non-inferiority analysis, and the sample size must be adequate to detect whether the high dose rifampin arms are non-inferior to standard 4R in terms of drug-related SAE.

As shown in Table 3 below, we expect the SAE rate with 4R to be 1% (as seen in the 4R vs 9H phase 3 trial) or 2% (as seen in the 4R vs 9H phase 2 trial), but have also included estimates if the SAE rate is as high as 3%. We define the maximum allowable (maximum tolerated) difference to be **4% more**. (*This is fairly stringent, but we believe a stringent non-inferiority margin is needed, since for an LTBI regimen to be acceptable, it is very important that the regimen is safe. Indeed safety is ESSENTIAL for an LTBI treatment regimen – as these are given to otherwise healthy persons.*) We must account for the clustering effect of households, since, as above, we expect that up to 65% of our participants will be HHC. However, in the just completed 4R vs 9H trial, the cluster effect (or ICC) in terms of serious AE was only 0.05, so the impact on sample size is much less than for completion.

**Table 3; Sample size required to conclude non-inferiority of** **2R_20,_ or 2R_30_ in terms of SAE compared to 4R (***Maximum tolerated difference = 4%)*

| Grade 3-5 Adverse event rate | | Number required per group to conclude non-inferiority. *(Assumes 4 contacts per HH, and ICC = 0.05)* | |
| --- | --- | --- | --- |
| **4R_10_** | **2R_20_ or 2R_30_** | N per arm | Total N – for 3 arms |
|  | | | |
| **1%** | **2%** | **234** | **702** |
|  | 3% | 698 | 2094 |
|  | 4% | 3468 | 10,404 |
|  | | | |
| **2%** | **3%** | **386** | **1158** |
|  | 4% | 1035 | 3105 |
|  | 5% | 4805 | 14,415 |
|  | | | |
| 3% | 4% | 534 | 1602 |
|  | 5% | 1366 | 4098 |
|  | 6% | 6114 | 18432 |

** In this table, for simplicity, all subjects are assumed to be HHC – since the ICC is low and has very modest effect on sample size required.*

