Table 3 shows that if SAE rate is only 1% in 4R_10_, and 2% in **2R_20_** or **2R_30_**, then we would need 234 patients per arm, or 702 patients in total to conclude that the high dose regimens were non-inferior to the standard dose for serious adverse events. But, if the real adverse event in the higher dose arms is 3% (ie 2% higher) then we would require 698 per arm, or 2,094 total participants. Hence, we run the risk of not having enough power to conclude non-inferiority if the actual serious adverse event rate is as little as 2% higher. This means we will ‘tolerate’ a very small excess in adverse events. If the actual SAE with **2R_20_** is 4% then the number needed to conclude non-inferiority increases even more markedly. On the other hand, if the SAE rate with 4R is actually 2% (as in phase 2) then the sample size required will be larger. But, with the 1359 anticipated enrolment needed to address our primary objective of completion, we should have adequate power to conclude non-inferiority if the high dose regimens have 3% rate (1% greater occurrence) of serious adverse events.

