# Randomization

Randomization will be by individual, except if there are more than one participant from the same household. If a HHC is enrolled and belongs to the same household as someone who has already been enrolled and randomized, that HHC (and all subsequent HHC from the same household) will be allocated to the same regimen *as long as they are enrolled within 14 days*. If they are enrolled later, they will be excluded. This is to avoid preferential enrollment of patients in the same household who may deem one regimen more attractive than the other, as was seen in our earlier 4R vs 9H trial.

Randomization will be computer generated and web-based. Investigators will enter all information from the initial case report form (baseline CRF). The randomization program will verify eligibility, and whether another member of the same household has already been randomized. Randomization will be in blocks of variable size, and stratified by country, and within Canada by city. The web based programme will be developed by collaborators ([name] and team) at the Laboratoire de télématique biomédicale (LTB) du Réseau en santé respiratoire du Québec (RSR), Sherbrooke, QC, who were responsible for all web-based data entry, randomization and adjudication panel work in our prior multi-centres trials (for demo see 2R^2^ link: [http://2r2-demo.crc.chus.qc.ca](http://2r2-demo.crc.chus.qc.ca/)  ID: 2r2demo Password: demo)

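### The randomisation strata should enter the primary completion model, and the safety upper limit should be a score-type limit at a named one-sided level

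*Protocol*

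**What the plan says.** Protocol, Statistical analysis, primary analysis 2: "Poisson regression will be used to compare the occurrence of the grade 3-5 adverse events between each of the two experimental arms" and the standard arm. Household clustering is handled by GEE "with an exchangeable correlation structure and empirical standard errors". Non-inferiority is judged by a confidence interval: the analysts will "compare the upper limit of the difference versus a margin of 4" per cent. No link, confidence level or sidedness is given. Primary analysis 1 (completion) does name an identity link.

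Protocol, Sample size considerations, sets the same margin: "We define the maximum allowable (maximum tolerated) difference to be 4% more". On the control rate it says "we expect the SAE rate with 4R to be 1% (as seen in the 4R vs 9H phase 3 trial) or 2" per cent (phase 2). Table 3 assumes four contacts per household and an ICC of 0.05, and gives 386 per arm for 2% versus 3% and 234 for 1% versus 2%. It states neither alpha nor power. The text then concludes that "we should have adequate power to conclude non-inferiority if the high dose regimens have 3% rate", that is, 1 point above a 2% control rate.

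Protocol, Randomization: allocation is "stratified by country, and within Canada by city". In Statistical analysis, both primary models name household clustering only. Site enters at one further place: "Sensitivity analyses will be conducted where by analysis are stratified by study centre and by country".

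**The concern.** Three things stand out.

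- **Strata.** Stratified randomisation removes between-stratum imbalance from the treatment comparison. A model without the strata still counts between-stratum variation in its standard error, so the completion comparison gives away precision that the design has already provided.
- **Upper limit.** Naming empirical standard errors, with no other interval method, implies a Wald limit. With very few control events such a limit tends to fall too low. Here that is the unsafe direction: a regimen exactly at the margin would be declared non-inferior too often, in people who are otherwise healthy.
- **Level.** The safety decision rule and Table 3 carry no error level, so a reader cannot tell whether the power statement refers to a 90% or a 95% interval.

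**Working it through.** **Inputs.** Margin 0.04; control rates 1% and 2%; four per household and ICC 0.05; 412 analysable and 453 enrolled per arm; 65% household contacts (all from Sample size considerations). The design effect is 1 + 3 × 0.05 = 1.15 if everyone is a household contact, as Table 3 assumes. At 65% it is 0.65 × 1.15 + 0.35 = 1.0975, about 1.10.

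**Step 1: reproduce Table 3.** On the risk-difference scale,

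n = DE × (z_α + z_β)² × [p1(1−p1) + p2(1−p2)] / (0.04 − (p2 − p1))².

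For 2% versus 3% the variance sum is 0.0196 + 0.0291 = 0.0487 and the distance to the margin is 0.03. For 1% versus 2% they are 0.0099 + 0.0196 = 0.0295 and 0.03.

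| Level, 80% power | (z_α + z_β)² | 2% vs 3% | 1% vs 2% |
|---|---|---|---|
| One-sided 5% | 6.18 | 385 | 233 |
| One-sided 2.5% | 7.85 | 488 | 296 |
| Table 3 | – | 386 | 234 |

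At one-sided 5% all nine rows of Table 3 agree within about 1%. At one-sided 2.5% none does. The alpha of 0.05 printed under Table 2 belongs to completion, and there it is two-sided: 7.85 × (0.1875 + 0.1275) / 0.10² = 247, the tabulated figure.

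**Step 2: power at 2% versus 3% with 412 per arm.** SE = √(DE × 0.0487 / 412), and power = Φ(0.03/SE − z_α).

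- DE 1.15: SE = 0.01166 and 0.03/SE = 2.573. Power is Φ(0.928) = 82% at one-sided 5% and Φ(0.613) = 73% at one-sided 2.5%.
- DE 1.0975: SE = 0.01139 and 0.03/SE = 2.634. Power is 84% and 75%.

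With all 453 analysable and a 95% interval, power is 77% (DE 1.15) or 79% (DE 1.0975). At 1% versus 2% with 412 per arm and DE 1.15, the same formula gives 91% even with a 95% interval.

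**Step 3: error of the Wald limit at the margin.** Expected control events are 412 × 0.01 = 4.1 up to 453 × 0.02 = 9.1. The simulation had 412 per arm, 65% of participants in households of four and ICC 0.05. It used a cluster-robust variance with independence weights as a stand-in for the exchangeable GEE.

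| True rates | Method | Nominal 5% | Nominal 2.5% |
|---|---|---|---|
| 1% vs 5% | Wald, clustered simulation | 7.0% | 4.1% |
| 2% vs 6% | Wald, clustered simulation | 6.2% | 3.4% |
| 1% vs 5% | Wald, exact binomial, no clustering | 6.6% | 3.6% |
| 2% vs 6% | Wald, exact binomial, no clustering | 5.8% | 3.2% |

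A score-type limit with variance inflated by the design effect gives 4.5-4.7% at nominal 5% and 2.1-2.4% at nominal 2.5%.

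**Step 4: price of the score-type limit.** At 2% versus 3%, 412 per arm and design effect about 1.10, simulated power goes from 83% (Wald) to 78% (score) at one-sided 5%, and from 75% to 67% at one-sided 2.5%.

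**Step 5: scale of the model.** A 4-point margin is a risk ratio of 0.05/0.01 = 5 at a 1% control rate and 0.06/0.02 = 3 at 2%. A ratio from a log link would therefore have to be converted before it could be compared with the margin. An identity link or marginal standardisation gives the difference.

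**Step 6: strata.** The Randomization section defines six strata: Indonesia, Vietnam and four Canadian cities. The Protocol gives no completion rates by site, so the gain from adjustment cannot be computed from it.

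**The case against.** The strongest reply is that little here is an error. The decision rule already refers to a difference, on the same scale as the margin, and a Poisson GEE can deliver one. Link, interval method and covariate list are commonly left to the SAP, which is not at hand. Nothing in the Protocol excludes stratum terms, and leaving them out generally makes the test conservative, not invalid. The Wald excess is modest, and the simulation uses independence weights instead of the planned exchangeable structure. No 95% interval is planned for safety, and at the one-sided 5% behind Table 3 the power statement holds.

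Much of this stands, and it rules out three stronger readings:

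- A reader might infer that the Poisson model contradicts the margin. The documents do not support this: no log link is stated and a difference is what is compared.
- A reader might infer that the power statement is false. It is true at one-sided 5% with the Wald formula; it fails only if a 95% interval is used.
- A reader might put a figure on the gain from stratum adjustment. A gain of about 4-14% in participants follows only if one assumes completion of 60-70% in Canada and 75-90% elsewhere. Those rates are not in the Protocol.

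The reply leaves three facts untouched. The Protocol places the strata in sensitivity analyses only. The standard errors it names lead to a limit that errs in the unsafe direction. Its power conclusion depends on a level that it does not name for safety.

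**Conclusion.** The point holds as two worthwhile improvements and a clarification; it does not make the analysis invalid.

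- **Completion:** the primary model should carry country and Canadian city. The gain is real in so far as completion differs between sites, but its size is unknown from the Protocol.
- **Safety limit:** the Wald limit is mildly anti-conservative, about 6-7% against 5% and 3-4% against 2.5%. This assumes control rates of 1-2%, ICC 0.05, 65% of participants in households of four, and independence weights as an approximation to the planned GEE.
- **Level and power:** Table 3 and the statement resting on it hold only at one-sided 5%, the upper limit of a 90% interval. At 2% versus 3% with 412 per arm, power is then about 82-84% (Wald) or 78% (score). With a 95% interval it is about 73-75% (Wald) or 67% (score), and the Table 3 formula needs about 488 per arm, above the 453 planned.

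**What to change.** 1. Include country and Canadian city in the primary completion model. If the identity link does not converge with these terms, obtain the risk difference by standardisation.
2. Take the safety upper limit from a score-type interval for the risk difference (Miettinen-Nurminen or Farrington-Manning) with cluster-inflated variance.
3. Name the one-sided level for safety, in the analysis section and under Table 3, and restate power for the interval actually used. With the score-type limit, quote 78% (one-sided 5%) or 67% (95% interval) at 2% versus 3%; the 82% and 73% figures belong to the Wald formula and should not be attached to a score interval.
4. Add one sentence saying that the Poisson GEE yields a risk difference, by identity link or standardisation.

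The cost is wording, some extra programming and about 5 points of power at one-sided 5% (83% to 78%). No change to the enrolment target is needed if one-sided 5% is openly adopted and 78% is accepted at 2% versus 3%.
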